### Baseline and Posttraining Data Collection

Before randomization, demographic information and self-reported questionnaires were collected from all participants at baseline. This information included participants’ sex, age, identity (student, resident, or HCP), education level (undergraduate or graduate degree), department affiliation (psychiatric or nonpsychiatric), and years of psychotherapy-related work. Additionally, outcome measurements were gathered, including trainees’ knowledge of psychotherapy, utilization of psychotherapy, self-reported self-efficacy, and self-reported motivation, among others. The questionnaires on psychotherapy knowledge, utilization, and self-efficacy and motivation to engage in psychotherapy were specifically designed based on our training program. Outcome measurements were assessed again 8 weeks after training (Table 1). Data were collected online using WenJuanXing (Questionnaire Star), a Chinese platform that provides professional online questionnaire surveys and data collection for RCTs [15]. The hospital’s data monitoring committee oversaw the data collection process, and personal information was deidentified to ensure confidentiality.

**Table 1 table1:** Schedule of enrollment and posttraining assessments.^a^

Schedule	Baseline	8 weeks after training
Initial approach	✓	N/A^b^
Informed consent	✓	N/A
Eligibility screen	✓	N/A
Randomization	✓	N/A
Intervention/control initiation	✓	N/A
Demographic characteristics	✓	N/A
Knowledge	✓	✓
Self-reported self-efficacy	✓	✓
Self-reported motivation	✓	✓
Utilization	✓	✓

^a^This table illustrates the schedule of enrollment and posttraining assessments. Initial approach, informed consent, eligibility screen, randomization, intervention/control initiation, and demographic characteristics were evaluated and collected only at the baseline timeline. Psychotherapy knowledge, self-reported self-efficacy, self-reported motivation, and utilization were both collected at the baseline and 8 weeks after the training.

^b^N/A: not applicable.

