**Results:**

A total of 160 participants were recruited and randomized between January 4 and 12, 2024. Baseline assessments were conducted from January 28 to February 1, 2024. The psychotherapy training program for the intervention group took place on February 3 and 4, 2024. Posttraining assessments were conducted starting April 1, 2024. Due to withdrawals, incomplete surveys, and data loss, we had a total of 113 participants: 57 in the intervention group and 56 in the control group. The amount of data varied across measures. The data analysis was finished in August 2024.

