### Recruitment

The researchers advertised the program online through the WeChat (Tencent Holdings Limited) official account of the Department of Psychiatry at Sir Run Run Shaw Hospital, Zhejiang University School of Medicine, to recruit potential participants. They encouraged sharing the program details with medical schools and hospitals. Interested individuals could register by sending messages and their identification to the research assistants ([name] and [name]). Research assistants then contacted the respondents to assess their eligibility, explain the study to each participant, and inform them about the allocation to either the control or intervention groups, where they would receive the psychotherapy training program.

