#### Intervention Group

All participants in the intervention group received the 2-day psychotherapy training program and were given a hard copy of the program booklet at recruitment. Additionally, supervision-based group meetings were held during the follow-ups at weeks 1, 2, 4, and 8, with each meeting lasting approximately 2 hours. During these follow-up meetings, instructors—including psychotherapists and psychiatrists—were available to answer any psychotherapy-related questions, encourage participants to practice psychological interventions, and provide further information to support the clinical application of psychotherapy.

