### Data Analysis

All data were automatically collected via WenJuanXing through a WeChat-based link. The data were downloaded from the WenJuanXing database into a user-specific Excel file. This study did not include interim analyses; data were analyzed only after all had been collected. The trial statistician blinded the intervention assignment in the data using R software (R Foundation for Statistical Computing) and SPSS (2013 release; IBM Corp.).

The primary hypothesis was that, compared with the control intervention, the intervention group receiving the psychotherapy teaching program would significantly gain more knowledge about psychotherapy after training. We also hypothesized that the program would lead to increased utilization of psychotherapy and be associated with improvements in knowledge. The third hypothesis posited that trainees’ self-reported self-efficacy and motivation to apply psychotherapy in clinical practice would increase significantly.

Descriptive statistics were used to assess demographic and psychotherapy-related characteristics at baseline. Following normality and homogeneity of variance tests, ANCOVA was used to analyze the primary outcomes. In the ANCOVA model, the dependent variable was the change in the knowledge score. The fixed factor was the group (intervention group or control group), while the covariates included the mean score of psychotherapy knowledge at baseline and years of psychotherapy experience. Pearson correlations and regression analysis (both linear and binary regression models) were used to explore factors associated with the knowledge score at baseline and to assess the increase in psychotherapy utilization in both the intervention and control groups. The secondary outcomes—participants’ psychotherapy utilization, confidence, and motivation—will also be analyzed in the same manner as knowledge.

A complete case analysis was performed, excluding any participants with missing information on the posttraining assessment. Additionally, a sensitivity analysis of the missing data was conducted to determine whether the missingness is random. Demographic information and scores for psychotherapy knowledge, utilization, confidence, and motivation at baseline were compared between the complete data group and the missing data group. All tests were 2-tailed, with a significance level set at *P*<.05.

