## Results

This study recruited 160 participants from January 4 to January 12, 2024. The 2-day training program took place on February 3 and February 4, 2024, and the posttraining assessment was completed on April 1, 2024. Due to withdrawals, incomplete surveys, and data loss, we had a total of 113 participants: 57 in the intervention group and 56 in the control group. The amount of data varies for each measure. Data analysis was completed in August 2024. The results will be published in peer-reviewed journals. If found to be effective, the psychotherapy training program and the accompanying program booklet will be made freely available to the public by the end of the trial.

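### The article places baseline before randomisation, but its own dates put baseline 16 to 28 days after; the true order decides whether the ANCOVA covariate is free of allocation effects

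*Protocol article*

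**What the plan says.** The protocol article gives two orders of events.

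- **Methods, Baseline and Posttraining Data Collection:** "Before randomization, demographic information and self-reported questionnaires were collected from all participants at baseline".
- **Abstract, Results:** "A total of 160 participants were recruited and randomized between January 4 and 12, 2024", and then "Baseline assessments were conducted from January 28 to February 1, 2024". Training came next: "The psychotherapy training program for the intervention group took place on February 3 and 4, 2024".

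Other sections bear on the order:

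- **Intervention Group:** participants in this arm "were given a hard copy of the program booklet at recruitment".
- **Control Group:** participants already allocated to the waitlist were messaged to complete the questionnaires from baseline to week 8. They received the booklet only after the posttraining measurement.
- **Recruitment:** research assistants were to explain the study and "inform them about the allocation to either the control or intervention groups".
- **Main Results section:** "This study recruited 160 participants from January 4 to January 12, 2024". This dates recruitment and does not mention randomisation.
- **Table 1:** randomisation and the baseline measures share one column.
- **Randomization and Group Allocation:** the timeline starts at the baseline assessment and does not say whether randomisation came before or after it.

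Under Data Analysis, the dependent variable is the change in knowledge score, and "the covariates included the mean score of psychotherapy knowledge at baseline and years of psychotherapy experience". Utilization, confidence and motivation are to be analysed in the same way.

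**The concern.** A baseline measured before randomisation cannot be affected by it, and this is what makes the baseline score a safe covariate. The Methods text gives that assurance and the abstract's dates contradict it.

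The assurance matters more than usual here. The primary measure is a 17-item self-rating of how well the participant knows each topic, and the questionnaire was built around the training program. The Discussion concedes that all measures are subjective and open to expectation. If people knew their arm, or one arm held the booklet, when they rated themselves, the two arms' baselines could differ because of allocation. Adjusting for such a score removes part of the effect or adds to it. The same would apply to the secondary outcomes analysed in the same way.

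**Working it through.** **1. The dates.**

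- Shortest possible gap from randomisation to baseline: January 12 to January 28 = 16 days.
- Longest possible gap: January 4 to February 1 = 28 days.
- Baseline to the first training day (February 3): 2 to 6 days.

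These are the limits of what individuals could have experienced; individual gaps are not given. The two windows do not overlap, so no participant can satisfy both statements.

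**2. Which order is likelier.** A message to people already allocated to control about questionnaires still to come, starting with baseline, fits allocation first. So does a booklet given at recruitment to one arm only, because handing it out requires a known allocation, and recruitment closed on January 12. Table 1 and the Randomization and Group Allocation section fit either order.

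**3. What a shifted baseline would do.** Let Δ be the true difference between arms in week-8 score, b the slope of week-8 score on baseline, and s the shift that allocation or the booklet causes in the intervention arm's baseline.

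- Week-8 score as outcome: estimate = Δ − b·s.
- Change as outcome, as planned: the arm difference in change is Δ − s and the slope of change on baseline is b − 1. The estimate is (Δ − s) − (b − 1)·s = Δ − b·s.

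The two are identical, so the covariate and the change score carry one bias, not two. A large simulation with Δ = 0.5, b = 0.5 and s = 0.2 gave 0.399 for both, against 0.5 − 0.5 × 0.2 = 0.40.

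**4. Illustration.** The plan's effect size of f = 0.25 corresponds, for two equal groups, to d = 2 × 0.25 = 0.50. The planned total of 128 reproduces (power 0.801) and is not in question. I take Δ = 0.50 SD. The document gives neither b nor s, so both are assumptions.

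| Assumed b | Assumed s (SD) | Estimate (SD) |
|---|---|---|
| 0.6 | +0.1 | 0.50 − 0.06 = 0.44 |
| 0.6 | +0.3 | 0.50 − 0.18 = 0.32 |
| 0.3 | +0.1 | 0.50 − 0.03 = 0.47 |
| 0.7 | +0.3 | 0.50 − 0.21 = 0.29 |
| 0.6 | −0.1 | 0.50 + 0.06 = 0.56 |
| 0.6 | −0.3 | 0.50 + 0.18 = 0.68 |

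A positive s would arise if reading the booklet raised self-ratings, and would hide benefit. A negative s would arise if people expecting training rated themselves lower beforehand, and would exaggerate it.

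**The case against.** The strongest reply is that the abstract may be the text in error. Randomisation is dated there and nowhere else, in a compressed sentence that joins it to recruitment, while the main Results section gives the same window for recruitment alone. If randomisation followed baseline, the Methods statement is right and no bias of this kind arises. This stands as a possibility. It would leave the one-arm booklet at recruitment and the message to allocated controls to be explained.

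A reader might go further and infer that the baseline was contaminated and the primary estimate is therefore biased. The document does not support that:

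- The Recruitment wording can mean only that participants were told they would be allocated to one of two groups. It does not show that each person learned their arm.
- No hand-out date is given for the booklet beyond the mention of recruitment, and nothing shows that it was read before the baseline form.
- All 160 are reported to have completed baseline, so there is no sign of loss between randomisation and baseline.
- The booklet mechanism would pull the estimate towards zero and would not create a false positive. Inflation needs an expectancy effect that the document does not describe.

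The contradiction between the Methods text and the abstract's dates survives all of this.

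**Conclusion.** The inconsistency is certain: the Methods text and the abstract's dates are incompatible, by 16 to 28 days. Allocation before baseline is the likelier order but is not established. The bias is conditional on that order and on allocation or the booklet having moved the self-ratings. Its form is −b·s, and its size and direction are unknown. An upward shift of 0.1 to 0.3 SD with a slope of 0.6, both assumed, would turn a true 0.50 SD into 0.44 to 0.32 SD. The point needs correcting because readers will rely on the stated order as protection for the primary covariate, and the article as written does not secure it.

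**What to change.** 1. Reconcile the abstract, Recruitment, Baseline and Posttraining Data Collection, Control Group, Intervention Group and Table 1. State the actual order and dates of randomisation, disclosure of allocation, booklet hand-out and baseline. If the abstract is wrong, correct it and explain the booklet timing.
2. If baseline followed allocation:
   - withdraw the statement that it came before randomisation;
   - report the baseline knowledge difference by arm;
   - beside the primary ANCOVA, report a sensitivity analysis of the week-8 knowledge score by arm, adjusted only for characteristics that allocation cannot change: years of experience, identity, education, department, age and sex.
3. Label that analysis post hoc, since data analysis was completed in August 2024.
4. Report both estimates without a rule that they must agree. If agreement meant that both are significant, power would fall from about 0.91 to about 0.74 (57 and 56 analysed, d = 0.5, assumed correlation 0.6, no contamination). That is a heavy price for an unproven bias.

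**Cost:** text corrections and one extra model on data already collected. The sensitivity model is less precise because it omits the baseline score. At an assumed correlation of 0.6 the residual SD with baseline is √(1 − 0.36) = 0.8 of that without it, so the standard error rises by a factor of 1/0.8 = 1.25, before any gain from the other covariates.

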### Development of the Psychotherapy Training Program

The psychotherapy training program was primarily developed by an experienced psychotherapist ([name]) and an MD-level psychiatrist ([name]), both of whom have approximately 20 years of relevant experience. The details of the 2-day psychotherapy training program are outlined in Multimedia Appendix 1. The program included 2 days of intensive training followed by 8 weeks of follow-up, with guidance on applying psychotherapy in clinical settings.

### Intervention

#### Control Group

After providing consent, participants allocated to the waitlist control group received a message encouraging them to complete all questionnaires from baseline through to the final follow-up at 8 weeks. They were sent messages via WeChat to thank them for their participation and to remind them of the timeline for completing the study. Once they finished the posttraining measurement, a digital booklet of the psychotherapy training program was provided to them via WeChat or as a hard copy upon request. After the trial concluded, participants in the control group were offered the opportunity to receive the psychotherapy training program free of charge.

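### The only stated missingness check ignores arm, although the conditions for completing week 8 differ by arm, so it can miss selection that would bias the completer comparison

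*Protocol article*

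**What the plan says.** **Booklet and contact.** Controls: "Once they finished the posttraining measurement, a digital booklet of the psychotherapy training program was provided to them" (Control Group). The same section adds that, after the trial, "participants in the control group were offered the opportunity to receive the psychotherapy training program free of charge"; no completion condition is attached to that offer. Intervention participants "were given a hard copy of the program booklet at recruitment" (Intervention Group) and had supervision meetings at weeks 1, 2, 4 and 8.

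**Analysis set.** "A complete case analysis was performed, excluding any participants with missing information on the posttraining assessment" (Data Analysis). The Results section gives 113 participants, "57 in the intervention group and 56 in the control group", from 160 recruited.

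**Missingness check.** "a sensitivity analysis of the missing data was conducted to determine whether the missingness is random" (Data Analysis). The method given is that demographics and baseline knowledge, utilization, confidence and motivation "were compared between the complete data group and the missing data group". Arm is not mentioned.

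**Adjustment.** In the primary model, "the covariates included the mean score of psychotherapy knowledge at baseline and years of psychotherapy experience". Baseline motivation, confidence and utilization are not in it.

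**The concern.** A completer comparison between arms is distorted when the kind of participant who completes differs by arm. Here there is a design reason to ask. For controls, the booklet follows completion. For the intervention arm, it came at the start, and contact with instructors continued to week 8. Different people may therefore have stayed in each arm.

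The stated check asks whether completers differ from non-completers overall. That averages the two within-arm differences, whereas the bias depends on how they differ from each other. A null result, together with almost identical completer counts, could be presented as evidence that loss was harmless when neither fact addresses the question. The outcomes are self-ratings, so motivation and confidence are plausible traits for selection to act on, and the primary ANCOVA does not adjust for them.

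**Working it through.** **Inputs.** Completers 57 and 56 (Results). 160 recruited, 1:1 allocation, about 80 per arm (Randomization and Group Allocation); exactly 80 and 80 is an assumption. Effect size f = 0.25, 128 required, 80% power (Sample Size and Power Calculation). The size and direction of selection, and the trait's correlation with knowledge change, are assumptions; the article gives no such figures.

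**The plan's own figure.** With noncentrality 0.25² × 128 = 8 and a two-sided 5% F test, power is 0.801, so 128 reproduces. For two equal groups d = 2f = 0.5 SD, which is used below only as a yardstick.

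**Loss by arm.** 80 − 57 = 23 (28.8%) and 80 − 56 = 24 (30.0%); together 47/160 = 29.4%. Fisher's exact p for the difference is 1.0. This says that equal numbers were lost, not that similar people were.

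**Completer imbalance on a baseline trait.** Let completers exceed non-completers by δ₁ in the intervention arm and δ₀ in the control arm, in SD units, with arms equal at randomization. The completer mean in each arm is then shifted by δ times the fraction lost:

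imbalance = δ₁ × 23/80 − δ₀ × 24/80

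| Assumed selection | Imbalance between completer groups | Arm-blind test significant | Arm-by-completion test significant |
|---|---|---|---|
| Exactly opposite (0.5, −0.5) | 0.144 + 0.150 = 0.29 SD | about 4–5% | about 82% |
| One arm only (0.5, 0) or (0, 0.5) | 0.14 or 0.15 SD in size | about 30% | about 30% |
| Same direction, equal (0.5, 0.5) | 0.006 SD in size | about 82% | about 5% |

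The test columns come from simulation with these counts and a within-arm SD of 1. In the first row, the overall completer-minus-non-completer difference is only about 0.01 SD, so the stated check sees nothing. In the third row it usually signals a difference although the between-arm comparison is almost unaffected. The check is thus least informative where the bias is largest.

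**From trait to outcome.** A trait imbalance becomes outcome bias only in proportion to its correlation with knowledge change. In a second simulation, retention depended on the trait with equal and opposite slopes by arm and there was no true effect. The within-arm differences were about ±0.47 SD. The imbalance is then 0.47 × 47/80 = 0.276 SD, and multiplying by correlations of 0.3 and 0.7 gives 0.08 and 0.19. The simulated bias was 0.09 to 0.19 SD, with type I error of 8% to 18%. This applies to a trait outside the ANCOVA.

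**The case against.** **Opposite selection is not shown.** A reader might infer that selection ran in opposite directions and cancelled. The documents do not support that. The natural mechanism points the same way in both arms: controls who still want the material and intervention participants who are still engaged are both the more interested ones. If that selection were equal, the imbalance would be near zero. This stands; the opposite case is a bound, not a prediction.

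**The incentive may be weak.** The booklet sentence may describe timing only, to keep controls unexposed until measured. Nothing says that non-completers were refused it, the later free course carries no stated condition, and reminders to non-completers are not limited by arm. This stands, and it is why the point rests on the check and not on the booklet.

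**The 0.29 SD could be misread.** A reader might set it against the 0.5 SD design effect as if it were bias. It is an imbalance on a baseline trait, and would equal outcome bias only at a correlation of 1. Selection acting through baseline knowledge or years of experience is largely handled by the ANCOVA.

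**The article may simply be condensed.** It does not call the comparison pooled, and a by-arm table could sit in a fuller document. That is possible. But the article states both the purpose (whether missingness is random) and the method (two groups defined by completeness), and that method, as written, does not serve that purpose for a between-arm comparison.

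**The by-arm test is not always better.** With selection in one arm only, it has about the same power as the arm-blind test, roughly 30%. This stands, so estimates by arm should be reported and a null test should not be read as clearance.

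**Conclusion.** The point holds as a limitation of the stated check, not as evidence of bias. Completion conditions differ by arm, 47 of 160 are excluded, and the check described cannot isolate arm-differential selection. Near-equal losses do not fill that gap.

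For an assumed 0.5 SD of selection, the completer imbalance ranges from near zero to 0.29 SD depending on direction. Outcome bias close to the upper end would be about 0.09 to 0.19 SD. These figures rest on an 80/80 split, on assumed selection sizes, and on a trait outside the model that correlates 0.3 to 0.7 with knowledge change. Selection on reactions after randomization, such as satisfaction with the course, could not be seen in baseline data even by arm.

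**What to change.** In Data Analysis:

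1. Compare baseline characteristics of completers and non-completers within each arm. Report the arm-by-completion contrast with confidence intervals for knowledge, utilization, confidence and motivation.
2. Add a baseline table of completers by arm.
3. Add a sensitivity ANCOVA with baseline motivation, confidence and utilization as covariates fixed in advance, not chosen by significance test.
4. Do not present equal losses plus a null arm-blind comparison as evidence that missingness is random.

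In the limitations, state that completion conditions differed by arm and that selection on post-randomization experience cannot be checked with baseline data.

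The cost is a few lines of analysis. The outcome sections report baseline questionnaires from all 160, so no new data are needed. The data analysis was finished in August 2024, so the additions should be labelled as post hoc where that applies. Changing when the booklet is released is no longer possible, because follow-up is over.
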